## Abstract

**Background:**

Tobacco use disorder (TUD) remains a global health crisis characterized by high relapse rates despite extensive cessation efforts. This study aims to enhance treatment outcomes by addressing the cognitive and neural imbalances associated with habitual and goal-directed behaviours among individuals with TUD. We hypothesise that by integrating high-intensity interval training (HIIT), cognitive remediation treatment (CRT) via app-based chess training and a standard smoking cessation program (SCP) for cognitive control and sleep quality will be improved, thereby facilitating smoking cessation.

**Methods:**

The study will enrol 140 treatment-seeking smokers aged 18–65 years who meet the DSM-5 criteria for TUD. The participants will be randomly assigned to four groups: CRT + HIIT in the morning, CRT + HIIT in the evening, HIIT alone in the morning, and HIIT alone in the evening. Assessments will be conducted at baseline (T1), postintervention (T2), and at a three-month follow-up (T3) at the Central Institute of Mental Health in Mannheim, Germany. The primary outcomes include abstinence days or amount of alcohol consumed in cases of relapse, as well as craving reduction. Secondary outcomes include improvements in cognitive functions (working memory, response inhibition, and cognitive control), measured through neuropsychological tasks, functional magnetic resonance imaging (fMRI), polysomnography, and self-report questionnaires. The repeated-measures design allows for within-subject comparisons to evaluate intervention effectiveness.

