**Fig. 1 Fig1:**
[figure not shown]
Schematic display of the study rational. The study aims to improve treatment outcomes in participants with TUD by enhancing cognitive control and sleep quality, thereby counteracting the hypothesised imbalance in regulatory control towards the habit system

We hypothesise that a combination of CRT and HIIT in the evening will enhance treatment outcomes to a greater extent than sleep enhancement via HIIT alone or a combination of CRT and HIIT in the morning. This will be reflected in more abstinence days or fewer cigarettes smoked following relapse. Furthermore, we hypothesise that improved cognitive control is mirrored in improved behavioral results in neuropsychological tasks and changes in neural activity, e.g., during tasks assessing response inhibition or working memory. We predict that these changes are associated with both craving and treatment outcomes.

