### Hypotheses

Primary hypotheses and treatment outcomes:

A combination of CRT + sleep enhancement (i.e., CRT + HIIT early evening) as a six-week add-on therapy enhances treatment outcomes (i.e., relapse and craving) in smokers in comparison to CRT (i.e., CRT + HIIT morning) or sleep enhancement (i.e., no CRT + HIIT early evening) alone.The changes in neural measures of response inhibition, working memory and network connectivity in the salience network following the six-week treatment from baseline will be associated with self-reported craving and perceived stress, as well as treatment outcomes.

2.Secondary hypotheses and mechanisms:

Improvement in cognitive function in smokers.

c.CRT, as a six-week add-on training, improves cognitive function in smokers (i.e., CRT + HIIT in the morning versus HIIT in the morning).

d.Sleep enhancement (induced by HIIT in the evening) as a six-week add-on training improves cognitive function in smokers (i.e., HIIT in the evening versus HIIT in the morning).e.The combined effect of sleep enhancement and CRT (i.e., the interaction effect of CRT × sleep enhancement) increases cognitive function even further.

Improvement in neuronal abnormalities.

f.CRT alleviates neural dysfunction during cognitive performance in smokers (i.e., CRT + HIIT in the morning versus HIIT in the morning).g.Sleep enhancement as a six-week add-on therapy ameliorates neural dysfunction during cognitive performance in smokers (i.e., HIIT in the evening versus HIIT in the morning), as reflected by neural measures of response inhibition, working memory and connectivity strength within the salience network.h.The combined effect of both training methods is even greater (i.e., the effect of CRT + HIIT in the evening versus HIIT in the morning).i.CRT as well as sleep enhancement (i.e., HIIT in the early evening) as a six-week add-on therapy reduces connectivity strength in the salience network.

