### Sample size

The sample size was calculated via the software package G*Power (version 3.1.9.4 [51]) on the basis of the number of days of abstinence at posttreatment (day 42). With a sample size of 128 participants (32 participants per group), we achieve a power of 80%, assuming a minimum effect size of f = 0.25 in an ANOVA at a 5% alpha level. This ensures an optimal balance of sample size, information gain, and resource allocation [52]. To account for potential dropouts, three participants per group will be added, resulting in a total population of 140 participants.

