### Statistical analyses

Primary outcome measures include [1] treatment outcome (i.e., abstinence rates) after a six-week intervention phase compared with baseline; [2] improvement in cognition and thus changes in neural measures of response inhibition, working memory and salience network connectivity in relation to craving, perceived stress and treatment success. After preprocessing, including movement correction and normalization to the Montreal Neurological Institute template, the echo planar images will undergo spatial smoothing with a Gaussian kernel of 8 mm full width at half maximum. The analysis will be conducted at both the single-subject and group levels via the general linear model approach. For resting-state analysis, the seed region is the right anterior insula for the salience network, which is one of the two core regions anchoring the salience network [95]. At the second level of analysis, paired t tests will be used to observe the effects of groups and time (preintervention vs. postintervention within one group). Additionally, full factorial models will be employed. Regression models incorporating various clinical variables, such as the severity of TUD, will also be calculated. Correction for statistical testing will be performed via familywise error correction at the level of *P* < 0.05. EEG data during sleep will be analysed via an in-house script in python, resulting in hypnograms and information, such as the timing and length of sleep stages, as well as spectrograms, including information on activation and frequency at specific electrodes.

SPSS (Statistics for Windows, IBM Corp., Armonk, NY) and R (R: A language and environment for statistical computing. R Foundation for Statistical Computing, Vienna, Austria) will be utilized to analyse physiological (e.g., heat rate during HIIT), psychometric (e.g., questionnaire data) and neuropsychological data. Multivariate analyses of variances with repeated measures will be conducted to analyse the dependent variables. Additionally, linear regression models will be employed to examine the influence of confounding variables on changes in the dependent variables. Finally, Cox regression analyses, such as examining brain activation in the dorsolateral prefrontal and/or inferior frontal regions during inhibition, will be performed to evaluate associations with possible relapse.

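### The primary outcome is stated differently in five places (once naming alcohol), while alpha and power are set for a single test

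*Protocol article*

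**What the plan says.** Five places in the protocol article describe the primary outcome.

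- **Abstract, Methods:** "The primary outcomes include abstinence days or amount of alcohol consumed in cases of relapse, as well as craving reduction". The next sentence puts cognition and imaging one level down: "Secondary outcomes include improvements in cognitive functions (working memory, response inhibition, and cognitive control".
- **Aims and objectives** (text after Fig. 1), on the main hypothesis: "This will be reflected in more abstinence days or fewer cigarettes smoked following relapse".
- **Hypotheses**, under the primary heading: evening CRT + HIIT "enhances treatment outcomes (i.e., relapse and craving) in smokers", against either of two comparators (morning CRT + HIIT; evening HIIT without CRT). A second primary hypothesis links neural change to craving, perceived stress and treatment outcome. Improvement in cognitive function is listed as secondary.
- **Sample size:** the calculation is made "on the basis of the number of days of abstinence at posttreatment (day 42".
- **Statistical analyses:** "Primary outcome measures include [1] treatment outcome (i.e., abstinence rates) after a six-week intervention phase compared with baseline", and as a second numbered primary item "improvement in cognition and thus changes in neural measures of response inhibition, working memory and salience network connectivity", to be related to craving, stress and treatment success.

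Table 1 lists four rows under outcome consumption: the Form 90 interview, time to relapse, days of abstinence and number of cigarettes. None of them is an alcohol outcome.

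**The concern.** Days abstinent, an abstinence rate, relapse, amount consumed after relapse and craving are different variables. They can give different answers in the same data. If the published sections disagree on which is primary, the result that counts as the trial's answer can be chosen after the data are seen.

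Two features of the Abstract's sentence add to this. It names the wrong substance. It also joins abstinence days to an amount that exists only in cases of relapse. Relapse happens after randomisation and is what the interventions are meant to change. Read literally, the second half compares groups selected by an effect of treatment, so it is not protected by randomisation.

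Finally, the 5% alpha and the power are attached to one ANOVA on one variable. They do not carry over to a set of primaries.

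**Working it through.** **Step 1. The sections side by side.**

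| Place | Behavioural outcome | Craving | Cognition / neural measures |
|---|---|---|---|
| Abstract | abstinence days, or alcohol amount if relapsed | primary | secondary |
| Aims and objectives | abstinence days, or cigarettes after relapse | correlate of the predicted changes | correlate of craving and outcome |
| Hypotheses | relapse | primary | cognitive gain secondary; neural associations primary |
| Sample size | days of abstinence, day 42 | not named | not named |
| Statistical analyses | abstinence rates at six weeks against baseline | correlate only | primary |

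No two rows agree fully. The Statistical analyses item is also worded as a change from baseline and names no contrast between arms.

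**Step 2. Alcohol.** Aims and objectives expresses the same idea with cigarettes, and Table 1 collects number of cigarettes. Elsewhere alcohol intake appears only as an exclusion criterion (Study population and design). The word is an error for cigarettes.

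**Step 3. Reproduce the stated sample size.** Inputs from Sample size: N = 128, 32 per group, f = 0.25, alpha 5%, power 80%. Noncentrality = N × f² = 128 × 0.0625 = 8; denominator df = 128 − 4 = 124.

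- Numerator df = 1 (a main effect or the interaction in the 2 × 2 layout): power 0.801, required N = 128. This reproduces the plan.
- Numerator df = 3 (four groups, one-way): power 0.639, required N = 179 (180 with equal groups). This does not.

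So the stated figure is for one outcome and one 1-df effect using all four arms.

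**Step 4. Several primaries, each at 5%.** The number k is assumed. Under independence, familywise error = 1 − 0.95^k. Power per outcome and N come from the Step 3 calculation with alpha = 0.05/k (Bonferroni).

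| k | Familywise error, each at 5% | Power per outcome at N = 128, Bonferroni | N for 80%, before dropout |
|---|---|---|---|
| 1 | 0.050 | 0.801 | 128 |
| 2 | 1 − 0.9025 = 0.0975 | 0.712 | 155 |
| 3 | 1 − 0.8574 = 0.143 | 0.656 | 171 |
| 4 | 1 − 0.8145 = 0.185 | 0.616 | 182 |

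For two-sided tests on jointly normal statistics, independence gives the largest familywise error, so the second column is a ceiling. As an example, take two outcomes by two comparators (k = 4). The comparisons share the evening CRT + HIIT arm, so with equal groups they correlate at 0.5. Simulation then gives about 17% if the two outcomes are uncorrelated and about 15% if they correlate at 0.7 (assumed values).

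**Step 5. One outcome, two comparators.** Unifying the outcome leaves two comparisons in Hypotheses. If success on either counts, each at 5%, familywise error is about 9% allowing for the shared arm (9.75% under independence). If both must succeed, there is no inflation but power is lower. With an assumed difference of 0.5 SD (f = 0.25 for two equal groups) and 32 per arm, the noncentrality is 0.5 × √(32/2) = 2.0. Power is 0.50 for one pairwise comparison. It is about 0.35 for winning both, by normal approximation with the two comparators equal. The choice of contrast therefore matters as much as the choice of outcome.

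**The case against.** The best defence is that the disagreement is narrower than five descriptions suggest. Hypotheses and Statistical analyses both give a two-part list, treatment outcome and then neural change in relation to craving, stress and treatment success, and these largely match. The Abstract is the main outlier, together with craving in the first primary hypothesis. That is fair. It still leaves days against rates, the changing status of craving and of cognition, and a sample size tied to only one of the variables.

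Four stronger readings are tempting, and the document does not support them.

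- **That no error rate is controlled.** A reader might infer this from the absence of any alpha allocation across primaries. The statistical analysis plan is not shown and may contain one, and Statistical analyses does state a familywise correction within its imaging text. What can be said is that alpha is set for one test while several primaries are named.
- **That familywise error is far above 18.5%.** A reader might count every pairing of a neural measure with a clinical variable as a confirmatory test. Nowhere does the article say that each is tested at 5% as a primary. Even the 10% to 18.5% range rests on an assumed count.
- **That a relapsers-only comparison is planned.** Statistical analyses specifies none, and Table 1 collects cigarettes in the intervention and follow-up phases without restriction to relapsers. The wording in the Abstract and in Aims and objectives invites such a comparison but does not establish it. No size of bias can be derived from the documents.
- **That alcohol is really an endpoint.** The article's own text and Table 1 resolve it as a slip. It changes nothing that is measured.

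It can also be said that several primaries are legitimate. They are, provided alpha is shared among them and power restated.

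**Conclusion.** The point holds as an internal contradiction. The article does not fix one primary outcome: the behavioural variable, the status of craving and the status of cognition change between sections, and the Abstract names the wrong substance. An analysis plan would not normally be left to settle contradictory published definitions.

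The stated N and power are correct for one outcome tested with one 1-df effect at 5%. If two to four primaries were each tested at 5%, familywise error would be at most about 10% to 18.5%; holding it at 5% by Bonferroni would lower power per outcome from 80% to between 71% and 62%. These figures assume the count and independence, and correlation lowers the error rate. They show what is at stake if the text stays as it is. They do not estimate the error rate of an analysis plan that is not shown.

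The relapse-conditional wording is a real weakness of definition, to be closed before analysis.

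**What to change.** 1. Use one primary outcome in the Abstract, Aims and objectives, Hypotheses, Sample size and Statistical analyses: number of days abstinent up to day 42, on which the sample size rests.
2. Name the contrast. For N = 128 to keep its 80% power it must be a single 1-df effect across the four arms. If the pairwise comparisons in Hypotheses are confirmatory instead, state whether both comparators must be beaten or how alpha is shared between them, and restate the power.
3. Replace alcohol with cigarettes in the Abstract.
4. List craving, cognition and the neural measures as secondary. Alternatively, keep some as primary with alpha explicitly allocated and power restated (N of 155, 171 or 182 before dropout for two, three or four outcomes under Bonferroni).
5. Define the consumption outcome over all randomised participants, with abstinent days counted as zero, and remove the restriction to cases of relapse.

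**Cost.** Items 1, 3 and 5 are wording; Table 1 already collects days of abstinence and number of cigarettes. Under the first option of item 4, craving, cognition and the neural measures lose primary status and N is unchanged. Sample size is affected only if several primaries or pairwise contrasts are kept as confirmatory.

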**Discussion:**

This study aims to provide insights into the mechanisms through which combined CRT and evening HIIT, alongside improvements in sleep quality, can enhance smoking cessation outcomes. The hypothesised benefits on cognitive control and neural activity changes are expected to support better treatment adherence and reduced relapse rates among individuals with TUD. Addressing potential challenges such as high dropout rates through comprehensive participant support is crucial for the study’s success. Findings from this research could inform future therapeutic strategies for TUD, potentially advancing addiction treatment approaches. The integration of novel interventions with established cessation programs underscores the study’s significance in exploring holistic approaches to improving public health outcomes related to tobacco addiction.

**Trial registration:**

Registered at clinicaltrials.gov/ct2/show/NCT05726045 (Date 04.04.2024).

**Supplementary Information:**

The online version contains supplementary material available at 10.1186/s40359-025-02482-w.

## Background

Tobacco is the second most commonly used psychoactive substance, with over one billion smokers worldwide [1]. With frequent use, nicotine, the addictive compound in tobacco, can lead to tobacco use disorder (TUD) [2]. Despite the known comorbidities associated with regular tobacco use as well as the desire to quit, many smokers encounter difficulties in doing so. Consequently, it is not surprising that approximately 75% of smokers who voluntarily attempt to quit relapse after six months [3]. This phenomenon may be attributed to an imbalance between the flexible goal-directed system and the more rigid habit system in individuals with TUD, leading to a continuation of smoking [4, 5]. This perspective suggests that addictive behavior arises through a transition from initially goal-directed (purposeful) smoking to habitual, and eventually compulsive, use [6]. This is underpinned by neural processes, namely a dysfunction in fronto-striatal circuitry ( [7, 8]). As such, prefrontal cognitive control mechanisms (e.g., in the dorsolateral prefrontal cortex (DLPFC) and inferior frontal gyrus (IFG)) support goal-directed behavior, whereas habitual behavior is underpinned by more dorsal networks, including the putamen and the premotor cortex ( [9–11]). Research has demonstrated that patients with substance use disorder (SUD) have reduced cognitive function in multiple domains, including working memory, inhibition, problem-solving, cognitive flexibility, and judgment formation [12], with cognitive decline and impairments also observed in heavy smokers [13].

The cognitive remediation treatment (CRT) approach is believed to enhance cognitive abilities related to the domains of inhibition, decision-making, working memory, cognitive flexibility, and attention [14]. In the past, CRT has been successfully used to treat subjects with SUD and therefore could also reduce habitual behavior in subjects with TUD [15, 16]. There is also significant evidence suggesting that playing the game of chess enhances cognitive control and inhibitory capacity in patients with schizophrenia by strengthening executive functions [17, 18]). Regular chess training has also been shown to improve the cognitive impairments associated with SUD, including problem-solving skills, mental flexibility, and working memory [19], with this training also requiring the use of abilities such as problem-solving, environmental awareness, and the ability to react to unexpected changes. Previous functional magnetic resonance imaging (fMRI) studies have revealed that the DLPFC, a region relevant to addictive behavior [11], as well as several other brain regions, including premotor, parietal, temporal, and occipital cortices, are activated when players are actively solving chess-related situations ( [20–22]). Building on previous studies involving subjects with cocaine use disorder, it may be conceivable that chess-based cognitive remediation treatment (CB-CRT) has the potential to enhance inhibitory control and executive function, leading to decreased impulsivity ( [23, 24]). Consequently, this reduction in impulsivity may positively impact therapy outcome measures, for example, through reducing the likelihood of relapse. Two addiction mechanisms have been proposed to further contribute to the understanding of differential therapy outcomes.

First, psychoactive substances, especially nicotine, can impact circadian rhythms through behavioral entrainment, thereby altering an individual’s optimum performance [25]. This alteration can lead to degraded alertness and attention through affecting the prefrontal cortex [26]. Previous studies have shown that sleep deprivation can increase smoking behavior and that the prevalence of sleep disturbances is greater among smokers ( [27, 28]). Sleep can be categorized into five stages: wakefulness, rapid eye movement (REM) sleep, and nonrapid-eye-movement (NREM) sleep [29]. Quiet wakefulness is characterized by a predominance of alpha waves, whereas REM sleep is characterized by mixed frequency, muscle atonia, and rapid eye movement. NREM sleep is described by slower frequencies, k-complexes, and large negative waves followed by a slower positive wave; NREM sleep can be referred to as slow-wave sleep (SWS) [30]. Both SWS and REM sleep are independently and homeostatically regulated and depend on an individual’s internal ‘circadian clock’ [31]. Studies have demonstrated that sleeping after exposure therapy results in better therapy outcomes ( [32, 33]), suggesting that therapy outcomes could be improved by improving sleep quality [34]. Memory consolidation processes occur during sleep after a new memory is acquired, leading to a transformation from transient to long-term memory storage due to the repeated replay of the learned trace ( [35–37]). Given the significance of sleep in addictive behavior and corresponding therapeutic interventions, it can be concluded that improved sleep quality may positively affect substance abstinence. On these grounds, a successful smoking cessation program should include interventions to enhance sleep quality [38]. Rodent studies have shown that this repeated replay in memory consolidation originates from the hippocampus and then spreads to other parts of the brain. In humans, sleep-dependent memory consolidation is suggested to originate from targeted memory consolidation [39–41].

Second, previous research has demonstrated a greater risk of developing cardiovascular diseases in individuals with SUD, which is attributed to regular substance use, poor nutrition, and obesity. To address this concern, high-intensity interval training (HIIT) can be administered as a therapeutic intervention. HIIT is a relatively short interval training involving interleaved, short blocks of exercises at high or low intensity. Its goal is to reach at least 80% of one´s maximum heart rate. Interestingly, study results indicate not only improved aerobic power and a decreased risk of developing lifestyle diseases but also enhanced inhibitory control as a result of HIIT interventions [42]. In addition, greater physical fitness has been associated with improved quality of life and reduced craving levels [43]. Observations suggest that HIIT has a beneficial effect on sleep quality and efficiency [44], as it has been observed that physical exercise has the potential to improve sleep [45]. Physical activity in the early evening can also lead to more time spent in NREM sleep, more slow waves, and increased sleep spindles, resulting in an enhanced opportunity for memory consolidation. Recent studies have shown that exercise intensity positively modulates the effect of memory consolidation and results in improvements in impaired sleep-dependent memory consolidation in schizophrenic patients ( [46, 47]). This makes HIIT an ideal candidate to promote memory consolidation indirectly by improving sleep quality.

Overall, add-on interventions to standard smoking-cessation programs, such as CRT, show promise in increasing the likelihood of tobacco abstinence through promoting the improvement of self-control via sleep-amplified memory consolidation of the interventions themselves.

